#### Safety

The safety of the study will be determined via incidence rates of all AEs and treatment-emergent AEs (TEAEs) from the time of SGM-101 administration through follow-up.

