The sensitivity will be based on the single lung nodule that is being removed in a patient. Typically for lung cancer surgery, we are there to remove one nodule. That will be the basis of the calculations. Thus, the denominator will be 10 patients for the first Cohort, and another 10 patients for the second Cohort. (A total of 20 data points for the whole study). The calculations will be based on two pieces of data: tumor fluorescence and pathology. We will not be doing a detailed IHC study at this time.

If successful, we will consider 10 more subjects. Then, with 20 subjects, we will have 90% power to identify any unforeseen adverse event that occurs with a prevalence of at least 5%. We will use a Bayesian continuous safety monitoring design that registers a signal if the posterior probability that the chance of an adverse reaction is greater than 0.1 exceeds 80%. If we encounter a safety signal, we will suspend enrollment until the issue has been addressed.

The fraction of tumors on pathology that are identified by the imaging procedure will provide an estimate of the sensitivity of the procedure. Of the 20 enrolled subjects, we expect approximately 60%, or 12, to have fluorescent tumors. With 12 tumors, an exact 95% confidence interval for sensitivity would range from (0%, 12%) if no tumors are detected up to (88%, 100%) if all 12 are detected. We will compute estimates of the sensitivity (fraction of path-positive margins that are called correctly) and specificity (fraction of path-negative margins that are called correctly), and calculate 95% confidence intervals around them. A second aim will be to estimate the sensitivity of the procedure for identifying all lesions, including lesions that were not pre-identified. Because some subjects will contribute more than one lesion, we will estimate these parameters using random effects logistic regression models (in SAS Proc Glimmix) that allow for between-subject variability. These specimens will provide independent estimates of the positive and negative predictive values of discovering satellite nodules.

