#### Adverse Event Reporting Period

The study period during which adverse events must be reported is from the time the subject checks-in for SGM 101 study dye infusion visit until completion of subject's post-operative visit (approximately 2-4 weeks after visit 3 date of surgery). The following common surgical adverse events with a start date occurring after the subject's surgical procedure has begun will not be captured unless the adverse event remains a grade 4 at discharge: pain, Nausea, Vomiting, Fatigue, Inflammation, Swelling, Tenderness at the site of incision, Pneumothorax, Atelectasis, Hemothorax,

Hydropneumothorax, Drain placement for fluid retention and air leak, Excision site pain, Atrial Fibrillation, Renal Insufficiency, Constipation, Anemia, Sinus Bradycardia, Crepitus, Stress, Urinary Retention, Drowsy, Light headedness, Headache, Pneumonia, Hypotension, Hypertension, Frustration, Irritability, Restlessness, and Insomnia.

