### 8.2 Recording of Adverse Events

At each contact with the subject while on the study, the investigator must seek information on adverse events by specific questioning and, as appropriate, by examination. Information on all adverse events should be recorded immediately in the source document, and also in the appropriate adverse event module of the case report form (CRF). All clearly related signs, symptoms, and abnormal diagnostic procedures results should be recorded in the source document, though should be grouped under one diagnosis.

The clinical course of each adverse event should be followed until resolution, stabilization, or until it has been determined that the study treatment or participation is not the cause. Serious adverse events that are still ongoing at the end of the study period must be followed up to determine the final outcome. Any serious adverse event that occurs after the study period and is considered to be related to the study treatment or study participation should be recorded and reported immediately.

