#### **8.4 Reporting SAE's to the DSMC**

All on-site SAEs for Penn subjects regardless of attribution or expectedness must be submitted to the DSMC within 10 days. Reports will be sent to the DSMC for **90 days** following the last date the subject received study treatment/therapy or was exposed to an investigational device.

All unexpected deaths or deaths related to the study agents/device must be reported within 24 hours. All other deaths should be reported within 30 days.

All adverse events which meet the following criteria will also be managed as described below:

All Grade 3 or higher events will be reported to the DSMC within 10 days of knowledge of the event. All unexpected deaths will be reported within 24 hours of knowledge of the event.

All other deaths will be reported within 30 days of knowledge of the event.

In addition, any adverse events will be recorded promptly in CTMS (clinical research management database).

In addition, any adverse events will be recorded in CTMS (clinical research management database).

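### Section 8.1 leaves 31 listed event types that start after surgery begins out of the AE data unless still grade 4 at discharge, contradicting the all-AE safety endpoint (3.2) and the recording and DSMC rules (8.2, 8.4)

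*Protocol*

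**What the plan says.** Four places in the protocol govern which adverse events are collected.

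- **Section 3.2, Safety.** The endpoint is "incidence rates of all AEs and treatment-emergent AEs (TEAEs) from the time of SGM-101 administration through follow-up". No event type is excepted.
- **Section 8.1, Adverse Event Reporting Period.** Collection runs from check-in for the infusion visit "until completion of subject's post-operative visit (approximately 2-4 weeks after visit 3 date of surgery"). A list of common surgical events follows. These "will not be captured unless the adverse event remains a grade 4 at discharge"; the rule applies to listed events "with a start date occurring after the subject's surgical procedure has begun". The list ends "Headache, Pneumonia, Hypotension, Hypertension, Frustration, Irritability, Restlessness, and Insomnia". Earlier entries include atrial fibrillation, renal insufficiency, anemia, sinus bradycardia and hemothorax.
- **Section 8.2.** "Information on all adverse events should be recorded immediately in the source document", and also in the CRF. Again there is no exception.
- **Section 8.4.** "All Grade 3 or higher events will be reported to the DSMC within 10 days of knowledge of the event". On-site SAEs also go to the DSMC within 10 days, whatever their cause and whether or not they were expected. Any adverse event is to be entered in CTMS.

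The Schedule of Procedures places AE assessments at the infusion, surgery and post-operative visits.

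**The concern.** The capture rule in 8.1 is narrower than the endpoint it feeds and narrower than two operating rules of the same protocol. A site that follows 8.1 does not collect what 3.2 says will be reported. A site that follows 8.2 and 8.4 does not apply 8.1.

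The exception is also tied to grade at one moment, discharge, rather than to the worst grade reached, and it has no test of relatedness. A listed event that the investigator attributes to SGM-101 is treated like any other.

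The study has no control group (Section 3.1), so the collected AE counts are the whole safety result. If the collection rule is ambiguous, nobody reading the reported incidence can tell which events it covers.

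**Working it through.** The protocol states no figure to reproduce here. The check is a count followed by a comparison of the sections.

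**Count of listed terms (8.1).** Counting comma-separated entries, with the drain-placement entry as one:
- from the first entry through drain placement: 12
- from excision-site pain through light-headedness: 11
- the last eight, from headache to insomnia: 8
- total: 12 + 11 + 8 = 31, all distinct.

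**What happens to a listed event that starts after surgery has begun.** The last four columns show what each rule requires.

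| Course of the event | Captured under 8.1 | In the 3.2 endpoint | Recorded under 8.2 | To DSMC under the 8.4 grade rule | In CTMS under 8.4 |
|---|---|---|---|---|---|
| Grade 1-2, before discharge | No | Yes | Yes | No | Yes |
| Grade 3, before discharge | No | Yes | Yes | Yes | Yes |
| Grade 4, improved by discharge | No | Yes | Yes | Yes | Yes |
| Grade 4, still so at discharge | Yes | Yes | Yes | Yes | Yes |
| Starts after discharge, before the post-operative visit | No: it cannot remain at a grade it had not yet reached | Yes | Yes | Yes if Grade 3 or higher | Yes |

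The rules agree in only one row of five. The last row matters because the reporting period runs about 2-4 weeks beyond surgery. Relatedness does not appear in the table because 8.1 does not use it.

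**Is there a reconciling clause?** The hospitalization paragraph of 8.1 allows the protocol to instruct otherwise, but that concerns whether a hospitalization is reported as an SAE. It does not amend 3.2, 8.2 or the Grade 3 rule in 8.4.

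**Reach.** Events between infusion and the start of surgery, and terms not on the list, are unaffected.

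**Size.** The protocol gives no expected rates for the listed events, so the understatement cannot be estimated. Its unit can be shown. If k of 20 subjects have a given listed event that goes uncaptured, the reported incidence of that term is too low by k/20. For k = 1 this is 1/20 = 5 percentage points, and for k = 4 it is 20 points. These values of k are illustrations. For these terms the error can only be downward.

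**The case against.** **The exclusion may be deliberate.** In an uncontrolled surgical study, expected operative morbidity cannot be separated from drug effect, and not collecting it is a legitimate choice. A specific rule can also be read as overriding general ones. This stands as a reason to keep some exemption. It does not settle the conflict, because nothing says which rule prevails and the endpoint still promises all adverse events.

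**Captured and reported may be different acts.** Hospital records are source documents (Section 9.2), so a site could notify the DSMC of a Grade 3 event without an AE-log entry. That is possible. But 8.2 names the CRF and 8.4 has any adverse event entered in CTMS, and the endpoint would be incomplete even on this reading.

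**A statistical analysis plan could define the endpoint.** It could restate the endpoint, but it cannot recover events never entered.

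Three stronger readings are tempting and are not supported.

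- *Deaths and serious events on the list disappear.* A reader might infer this because a fatal event does not remain grade 4 at discharge. But all deaths go to the IRB (24 or 72 hours, Section 8.3) and to the DSMC (24 hours or 30 days, Section 8.4). On-site SAEs go to the DSMC, unexpected related events to the IRB, and attributable SAEs to the pharmacovigilance company. None of these routes is limited to events captured under 8.1. They do not, however, cover non-serious events below Grade 3 that are expected or not attributed to the research.
- *The Bayesian safety rule runs on incomplete counts.* Section 7.1 says that it "registers a signal if the posterior probability that the chance of an adverse reaction is greater than 0.1 exceeds 80"%. The term adverse reaction is not defined, so whether it draws on the 8.1 data is unknown.
- *Drug remaining at surgery shows that drug effects are missed.* With the preliminary mean half-life of about 30 h (Section 1.2) and single-exponential decline, the fraction left is 0.5^(hours/30): 19% at 3 days and 6% at 5 days, or 33% and 4% at the 2 and 6 days that the one-day window in 5.2 allows. Exposure is not nil, but these percentages measure neither missed events nor causation.

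**Conclusion.** The contradiction is real and should be corrected. As written, the AE data would cover a subset of adverse events while Section 3.2 promises all of them. Incidence for the 31 listed terms would be understated by an amount the protocol gives no means of estimating.

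For listed events of Grade 3 or higher, the capture rule in 8.1 and the reporting and CTMS rules in 8.4 are not reconciled. This rests on reading 8.1 literally and on the absence of any clause giving one section precedence.

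The conclusion stops there. It does not extend to unreported deaths or SAEs, to a failure of the Bayesian rule, or to evidence of a missed drug effect.

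**What to change.** Reconcile the sections around one exception, stated once and cited elsewhere.

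- **8.1:** *A listed event that starts after surgery has begun is exempt from capture only if its maximum grade is 1 or 2, it is not serious, and it is judged unrelated to SGM-101. Every other listed event is captured at its maximum grade, whether it starts before or after discharge.*
- **3.2:** *Incidence of all AEs except those exempted in 8.1.*
- **8.2 and the CTMS sentence of 8.4:** add a cross-reference to the 8.1 exemption.
- **8.4, Grade 3 or higher and SAE rules:** no change, since the exemption no longer touches them.

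Two details need care. The limit to onset after surgery has begun must stay, or mild events on the infusion day that are collected now would be lost. The exception in 3.2 must be identical to that in 8.1, or possibly related or serious listed events would be collected but left out of the endpoint.

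The cost is protocol wording, a grade and relatedness judgment for listed events, and some more AE entries from hospital records already available. No visit or procedure is added, because the post-operative visit already includes an AE assessment.

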#### Preexisting Condition

A preexisting condition is one that is present at the start of the study. A preexisting condition should be recorded as an adverse event if the frequency, intensity, or the character of the condition worsens during the study period.

#### General Physical Examination Findings

At screening, any clinically significant abnormality should be recorded as a preexisting condition. At the end of the study, any new clinically significant findings/abnormalities that meet the definition of an adverse event must also be recorded and documented as an adverse event.

#### Post-study Adverse Event

All unresolved adverse events should be followed by the investigator until the events are resolved, the subject is lost to follow-up, or the adverse event is otherwise explained. At the last scheduled visit, the investigator should instruct each subject to report any subsequent event(s) that the subject, or the subject's personal physician, believes might reasonably be related to participation in this study.

#### Abnormal Laboratory Values

A clinical laboratory abnormality should be documented as an adverse event if any one of the following conditions is met:

1. The laboratory abnormality is not otherwise refuted by a repeat test to confirm the abnormality
2. The abnormality suggests a disease and/or organ toxicity
3. The abnormality is of a degree that requires active management; e.g. change of dose, discontinuation of the drug, more frequent follow-up assessments, further diagnostic investigation, etc.
4. The post-surgical laboratory abnormality falls outside the following ranges:
  - a. Glucose: 50-500mg/dl
  - b. Red Blood [contact] MII/uL
  - c. Hemoglobin: 6.75-20.00g/dL
  - d. Hematocrit: 20.0-60.0%
  - e. Creatinine: 0.3-5.0mg/dL
  - f. Sodium Level: 110-180mmol/L
  - g. Potassium Level: 2.5-8.0mmol/L
  - h. Chloride: 80-150 mmol/L
  - i. CO2: 10-60mmol/L
  - j. Calcium Level: 6.0-20.0 mg/dL

5.

### Hospitalization, Prolonged Hospitalization or Surgery

---

Any adverse event that results in hospitalization or prolonged hospitalization should be documented and reported as a serious adverse event unless specifically instructed otherwise in this protocol. Any condition responsible for surgery should be documented as an adverse event if the condition meets the criteria for an adverse event. Neither the condition, hospitalization, prolonged hospitalization, nor surgery are reported as an adverse event in the following circumstances:

1. Hospitalization or prolonged hospitalization for diagnostic or elective surgical procedures for a preexisting condition.
2. Surgery should not be reported as an outcome of an adverse event if the purpose of the surgery was elective or diagnostic and the outcome was uneventful.
3. Hospitalization or prolonged hospitalization required to allow efficacy measurement for the study.
4. Hospitalization or prolonged hospitalization for therapy of the target disease of the study, unless it is a worsening or increase in frequency of hospital admissions as judged by the clinical investigator.

### 8.2 Recording of Adverse Events

At each contact with the subject while on the study, the investigator must seek information on adverse events by specific questioning and, as appropriate, by examination. Information on all adverse events should be recorded immediately in the source document, and also in the appropriate adverse event module of the case report form (CRF). All clearly related signs, symptoms, and abnormal diagnostic procedures results should be recorded in the source document, though should be grouped under one diagnosis.

The clinical course of each adverse event should be followed until resolution, stabilization, or until it has been determined that the study treatment or participation is not the cause. Serious adverse events that are still ongoing at the end of the study period must be followed up to determine the final outcome. Any serious adverse event that occurs after the study period and is considered to be related to the study treatment or study participation should be recorded and reported immediately.

### 8.3 Reporting of Serious Adverse Events and Unanticipated Problems

Investigators must conform to the adverse event reporting timelines, formats and requirements of the UPenn IRB (8.3.1) and DSMC (8.4) to which are responsible, but at a minimum those events that must be reported are those that are:

1. related to study participation,
2. unexpected, and
3. serious or involve risks to subjects or others (see definitions, section 8.1).

If the report is supplied as a narrative, the minimum necessary information to be provided at the time of the initial report includes:

1. Study identifier
2. Study Center
3. Subject number
4. A description of the event
5. Date of onset
6. Current status
7. Whether study treatment was discontinued
8. The reason why the event is classified as serious
9. Investigator assessment of the association between the event and study treatment

#### Investigator reporting: notifying the Penn IRB

This section describes the requirements for safety reporting by investigators who are Penn faculty, affiliated with a Penn research site, or otherwise responsible for safety reporting to the Penn IRB. The University of Pennsylvania IRB (Penn IRB) requires expedited reporting of those events related to study participation that are unforeseen and indicate that participants or others are at increased risk of harm.

The Penn IRB will not acknowledge safety reports or bulk adverse event submissions that do not meet the criteria outlined below. The Penn IRB requires researchers to submit reports of the following problems within 10 working days from the time the investigator becomes aware of the event: Any adverse event (regardless of whether the event is serious or non-serious, on-site or off-site) that occurs any time during or after the research study, which in the opinion of the principal investigator is:

Unexpected (An event is “unexpected” when its specificity and severity are not accurately reflected in the protocol-related documents, such as the IRB-approved research protocol, any applicable investigator brochure, and the current IRB-approved informed consent document and other relevant sources of information, such as product labeling and package inserts.) AND Related to the research procedures (An event is “related to the research procedures” if in the opinion of the principal investigator, the event was more likely than not to be caused by the research procedures.

#### Investigator reporting: notifying the Pharmacovigilance company

All attributable SAEs will be reported to Vigipharm, the Pharmacovigilance company, that monitors the use of SGM-101.

#### Reporting Process

Unanticipated problems posing risks to subjects or others as noted above will be reported to the Penn IRB using the form: “Unanticipated Problems Posing Risks to

Subjects or Others Including Reportable Adverse Events” or as a written report of the event (including a description of the event with information regarding its fulfillment of the above criteria, follow-up/resolution and need for revision to consent form and/or other study documentation).

Copies of each report and documentation of IRB notification and receipt will be kept in the Clinical Investigator’s study file.

#### Reporting Deaths: more rapid reporting requirements

Concerning deaths that occur during the course of a research study, the following describes the more rapid reporting requirement of the Penn IRB for specific situations:

- Report the event within 24 hours when the death is unforeseen (unexpected) and indicates participants or others are at increased risk of harm.
- Report the event within 72 hours, for all other deaths, regardless of whether the death is related to study participation.

For reportable deaths, the initial submission to the Penn IRB may be made by contacting the IRB Director or Associate Director. The AE/Unanticipated Problem Form is required as a follow up to the initial submission.

#### Other Reportable events:

For clinical drug trials, the following events are also reportable to the Penn IRB:

- Any adverse experience that, even without detailed analysis, represents a serious unexpected adverse event that is rare in the absence of drug exposure (such as agranulocytosis, hepatic necrosis, Stevens-Johnson syndrome).
- Any adverse event that would cause the investigator to modify the protocol or informed consent form, or would prompt other action by the IRB to assure protection of human subjects.
- Information that indicates a change to the risks or potential benefits of the research, in terms of severity or frequency. For example:
  - An interim analysis indicates that participants have a lower rate of response to treatment than initially expected.
  - Safety monitoring indicates that a particular side effect is more severe, or more frequent than initially expected.
  - A paper is published from another study that shows that an arm of your research study is of no therapeutic value.
- Change in FDA safety labeling or withdrawal from marketing of a drug, device, or biologic used in a research protocol.
- Breach of confidentiality
- Change to the protocol taken without prior IRB review to eliminate apparent immediate hazard to a research participant.
- Incarceration of a participant when the research was not previously approved under Subpart C and the investigator believes it is in the best interest of the subject to remain on the study.

- Complaint of a participant when the complaint indicates unexpected risks or the complaint cannot be resolved by the research team.
- Protocol violation (meaning an accidental or unintentional deviation from the IRB approved protocol) that in the opinion of the investigator placed one or more participants at increased risk, or affects the rights or welfare of subjects.

